#### Blinding

Neither the participants nor the investigators and assessors of outcomes can be blinded to allocation because of the nature of service delivery that will be provided, and thus, we are obliged to make the randomized controlled trial nonblinded; however, it should be mentioned that the outcomes of the trial are objective in nature, therefore, the risk of bias is minimal. Furthermore, the randomization, as well as statistical analysis, will be carried out by someone unconnected to the enrollment process.

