In conventional practice, pregnant women are evaluated for hypertensive disorders or associated complications during routine antenatal care visits. Standard antenatal care practices often delay or miss detecting hypertensive disorders during pregnancy, which may allow the women to become vulnerable to the adverse consequences of hypertensive disorders. Although, over the last two decades in Bangladesh, there has been an increase in the occurrence of at least one antenatal care (78%) visit during pregnancy, only 31% of women attend the recommended 4 antenatal care visits [6]. Furthermore, the quality of health care, which is fundamental to translating use of antenatal care services into improved maternal and fetal health outcomes, is generally poor in Bangladesh [5]. Weight and blood pressure measurements are two essential components of antenatal care services and should be ensured for quality care. Monitoring weight gain is important because both inadequate and excessive weight gain during pregnancy have been associated with an increased risk of developing hypertensive disorders [9,10]. To achieve an optimal pregnancy outcome, the United States Institute of Medicine provided recommendations for gestational weight gain stratified according to prepregnancy body mass index (BMI). The 2009 US Institute of Medicine guidelines on total gestational weight gain suggest that women who are underweight (BMI less than 18.5 kg/m^2^), normal weight (BMI from 18.5 to 24.9 kg/m^2^), overweight (BMI from 25.0 to 29.9 kg/m^2^) or obese (BMI greater than or equal to 30.0 kg/m^2^) should gain from 12.5 to 18 kg, 11.5 to 16 kg, 7 to 11.5 kg, and 5 to 9 kg, respectively. The recommendations for rates of weight gain during the 2nd and 3rd trimester are 0.51 (range 0.44-0.58) kg/week, 0.42 (range 0.35-0.50) kg/week, 0.28 (range 0.23-0.33) kg/week and 0.22 (range 0.17-0.27) kg/week, respectively, for the same BMI stratification [11]. As blood pressure has a property of circadian and other temporal variations, the current blood pressure measurement practices, which are also subject to interclinician and terminal digit bias, result in misdiagnosis [12]. A better method of hypertension diagnosis in women makes use of multiple measurements taken over continuous monitoring of blood pressure. While 24-hour ambulatory blood pressure monitoring could be an option, it can cause discomfort, particularly during pregnancy and is limited to only 24 to 48 hours of continuous monitoring [13]. In contrast, physiological parameter–derived blood pressure measurement is novel, noninvasive, and convenient to regularly monitor blood pressure. Blood pressure is estimated through linear modeling of extracted physiological parameters and machine learning algorithms that use features such as electrocardiogram (ECG) and photoplethysmography (PPG) derived pulse width and pulse transit time. Health Gauge is an affordable, wrist-worn wearable device that uses pulse width and pulse transit time to provide blood pressure measurements and is convenient for obtaining a picture of blood pressure and heart rate variability over time (Figure 1). Other methods, such as uterine artery Doppler ultrasonography and maternal blood concentrations of angiogenic factors and metabolomics, are also available to predict and monitor hypertension in pregnancy [14]; however, these tools are more expensive and less convenient for use in resource-poor settings including Bangladesh.

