#### Intervention

Before 20 weeks of gestation, each woman in the intervention arm will be provided with a Health Gauge device and with a smartphone, if she does not already have one. The app for Health Gauge will be installed on each participant’s smartphone. The women will be asked to use the Health Gauge device and app to measure their blood pressure at least two times a day (morning and evening), starting from 20 weeks of gestation. The blood pressure measurement records will be automatically stored in the smartphone app. Participants will be trained to charge and operate the Health Gauge device. Most women in rural Matlab do not have internet access. Hence, trained health workers will visit the women weekly and synchronize the smartphones with tablet computers to collect the stored data and to upload the data to an online server. The health workers will also measure the weight of the participant using a digital weighing scale every month. If any woman is found to be hypertensive (blood pressure is greater than or equal to 140/90 mmHg on two consecutive measurements), is presenting signs and symptoms associated with hypertensive disorders or associated complications (described later), or is gaining weight outside of the applicable US Institute of Medicine recommended range [11], she will be advised to visit Matlab hospital (icddr,b) or a government health facility immediately for further evaluation and management. If the condition demands, our health worker will ensure that an appropriate referral is made to a tertiary health care facility. This intervention will be in addition to the conventional programs offered by icddr,b as well as government health facilities.

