#### Control

All women randomized to the control arm will receive standard antenatal care. In addition, health workers will visit the women every two months starting from 20 weeks of gestation to measure their weight using a digital weighing scale. If any woman is gaining weight outside of the applicable US Institute of Medicine recommended range, she will be advised to visit Matlab hospital (icddr,b) or a government health facility immediately for further evaluation and management. If the condition demands, our health workers will ensure that an appropriate referral is made to a tertiary health care facility.

Health workers will counsel all participants, both in the intervention and in the control group, to make at least four antenatal visits. All women will be provided with general education to maintain a balanced diet and to remain physically active during pregnancy.

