#### Participant Enrollment and Follow-up

In Matlab, pregnancies are usually diagnosed by 12 weeks of gestation and recorded by Health and Demographic Surveillance System field staff. We will obtain this information from Health and Demographic Surveillance System and conduct baseline interviews to identify eligible participants for this study. Health worker will continue to conduct baseline interviews and enroll participants whenever newly pregnant women are identified, and to obtain information from the Health and Demographic Surveillance System until the desired sample size is met. Each potential participant will be provided with a consent form in the local language (Bengali). Health worker will also explain the study in detail and answer any questions. If a woman agrees to participate in the study, her signature or left thumb impression and that of a witness will be taken. A health worker will also sign the consent form in front of the woman and the witness on behalf of the principal investigator of the study. Then the health worker will conduct a short interview using a semistructured questionnaire and record the woman’s height and weight. If eligibility criteria are satisfied, the health worker will open the sealed envelope (in sequence and in front of the participant and the witness) that assigns the participant to the allocated group (intervention or control). If the woman does not meet the eligibility criteria, she will be informed that she cannot take part in the study.

Once enrolled, the women will be followed from 20 weeks of pregnancy until delivery. Health worker will visit women in the intervention arm weekly and those in the control arm every two months. Furthermore, health workers will maintain mobile communication with all women to keep track of the progress of the pregnancy. Health worker will collect outcome data from the households and health facilities by follow-up visit or by phone.

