##### Follow-up Questionnaire

Health worker will administer a follow-up questionnaire weekly to the women in the intervention group to collect information on signs and symptoms associated with hypertensive disorders and complications, including sense of awareness, headache, blurring of vision, abdominal pain, nausea and vomiting, edema, and convulsions over the previous week.

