##### Secondary

Clinical outcomes will be rate of weight gain during pregnancy; infant weight, length, and head circumference at birth; hypertension status; adverse consequences of hypertensive disorders; blood pressure profile and heart rate; risk factors; and serious adverse events. Rate of weight gain during pregnancy will be measured in kilograms per week and be calculated by subtracting the baseline (enrollment) weight from the predelivery weight and dividing that value by the number of weeks between the two time points. Infant weight will be measured in grams, infant length will be measured in centimeters, and head circumference at birth will be measured in centimeters. The number of women with chronic hypertension and who develop hypertensive disorders will be recorded. Adverse consequences of hypertensive disorders of pregnancy will be defined as maternal or fetal complications or consequences that arise in a woman with chronic hypertension or in a previously normotensive woman who has developed some form of hypertensive disorder after at least 7 days of intervention. Maternal complications are abruptio placentae, disseminated coagulopathy or hemolysis, elevated liver enzymes and low platelets syndrome, pulmonary edema, acute kidney injury, eclampsia, liver failure or hemorrhage, stroke, or death. Fetal or neonatal complications are intrauterine death or stillbirth, preterm birth, small for gestational age, low birth weight, hypoxic brain injury, and complications associated with small for gestational age, low birth weight, or prematurity. Episodes, type, and timing of occurrence of adverse consequences will be reported. The blood pressure profile along with heart rate from 20 weeks of pregnancy until delivery will be recorded. The prevalence of specific risk factors along with the sociodemographic profile of the participants will be determined. We do not anticipate any serious adverse events in this trial; however, should any other adverse events arise they will be reported in detail.

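### Hypertensive disorders are looked for far more intensively in the intervention arm than in the control arm, so the claim of objective outcomes and minimal bias does not hold for hypertension status or its adverse consequences

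*Protocol article*

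**What the plan says.** The Blinding section states that "Neither the participants nor the investigators and assessors of outcomes can be blinded to allocation", and offers as reassurance that "the outcomes of the trial are objective in nature, therefore, the risk of bias is minimal".

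The clinical outcomes (Outcome Measures, Secondary) include:
- **Hypertension status:** "The number of women with chronic hypertension and who develop hypertensive disorders will be recorded".
- **Blood pressure profile and heart rate**, from 20 weeks to delivery.
- **Adverse consequences of hypertensive disorders.** These are counted only in women with chronic hypertension, or in previously normotensive women who develop a hypertensive disorder once seven or more days of intervention have passed.

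Data Analysis plans no hypothesis tests, but does plan effect estimates with 95% confidence intervals on clinical outcomes, measured as the definitive trial would probably measure them.

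By arm:
- **Intervention.** Women are asked to "measure their blood pressure at least two times a day (morning and evening), starting from 20 weeks of gestation". Health workers visit weekly, and "Health worker will administer a follow-up questionnaire weekly to the women in the intervention group" about signs and symptoms. Two consecutive readings at or above 140/90 mmHg, symptoms, or weight gain outside the recommended range each lead to advice to attend a facility.
- **Control.** Besides standard antenatal care, "health workers will visit the women every two months starting from 20 weeks of gestation to measure their weight". Weight gain is the only study referral trigger described. No study blood pressure reading and no symptom questionnaire are described.

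**The concern.** An objective instrument protects against bias in reading a value. It does not protect against bias in who is measured, or how often. Here the study's own blood pressure measurement and symptom enquiry are applied to one arm, so the same underlying disease has many more chances to be found there.

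Three outcomes are touched:
- **Hypertension status** depends directly on detection.
- **Adverse consequences** depend on it at one remove. Complications in a control woman whose hypertension was never found drop out of the count. The seven-day qualifying period is tied to the intervention and has no control counterpart.
- **Blood pressure profile and heart rate** have no described source in the control arm.

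At stake is what the pilot may conclude. A raised count in the intervention arm could be reported as an effect estimate, or carried into the definitive trial as an incidence rate, when it may only reflect how hard each arm was searched. The sentence on minimal bias would support that misreading in the pilot report.

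**Working it through.** **1. Scheduled device readings, intervention arm.** Inputs: at least 2 readings a day from 20 weeks (Intervention); follow-up to delivery, since "the women will be followed from 20 weeks of pregnancy until delivery" (Participant Enrollment and Follow-up). Gestation at delivery is not given, so 37 to 41 weeks is assumed, with full adherence.

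Readings = 2 × 7 × (weeks at delivery − 20)
- 37 weeks: 2 × 7 × 17 = 238
- 39 weeks: 2 × 7 × 19 = 266
- 41 weeks: 2 × 7 × 21 = 294

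The article states no such total, so there is no plan figure to reproduce.

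**2. Blood pressure opportunities, control arm.** The conventional schedule in the Intervention section has three visits after 20 weeks (24 to 26, 32, and 36 to 38 weeks), plus one at 41 weeks if undelivered. At 266 against 3, the ratio is about 89 to 1. This is only a guide, because that schedule is for women without major risk factors and all trial women are classed as high-risk. The true number of control readings is unknown. Intervention women receive antenatal care too. Background adds that nationally "only 31% of women attend the recommended 4 antenatal care visits", and that standard antenatal care often delays or misses detection.

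**3. Can the unequal search create a difference when blood pressure is the same in both arms?** This illustration uses the systolic part of the two-consecutive-readings rule. Assumptions not in the article: a normotensive woman with true mean 115 or 120 mmHg, total reading SD 10 or 12 mmHg, and 266 readings.

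Per-reading exceedance is q = P(Z ≥ (140 − mean)/SD). The chance of at least one run of two comes from an exact recursion over the 266 readings. For independent readings it is close to 1 − exp(−265q²). The control comparator is four visits with one repeat each: 1 − (1 − q²)⁴ when independent.

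| Mean, SD | q | 266 readings, independent | 266 readings, lag-1 correlation 0.3 (simulated) | Four visits with repeat, independent | Four visits with repeat, correlation 0.3 |
|---|---|---|---|---|---|
| 115, 10 | 0.0062 | 1.0% | about 6% | 0.02% | 0.1% |
| 115, 12 | 0.0186 | 8.6% | about 30% | 0.1% | 0.6% |
| 120, 10 | 0.0228 | 12.6% | about 39% | 0.2% | 0.8% |
| 120, 12 | 0.0478 | 44.0% | about 78% | 0.9% | 2.6% |

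Sensitivity:
- Half adherence (133 independent readings) gives 0.5% to 25% in the intervention arm.
- A within-visit correlation of 0.8 raises the highest control figure to about 9%.
- In the lowest scenario, 1% of 35 women is 0.35 of a woman; in the highest independent scenario, 44% of 35 is about 15.

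**4. What step 3 does and does not show.** The rule modelled is the trigger for sending a woman to a facility. The Secondary outcomes section does not adopt it as the definition of hypertension status. The percentages are therefore chances of crossing an alert, not of being counted as a case. They show that unequal search can produce a difference without any true effect, and in which direction. They do not estimate the bias in the reported outcome.

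**5. If only facility diagnoses count.** The imbalance remains. Device readings and weekly symptom enquiry send intervention women to facilities, while the only study trigger in the control arm is weight, checked every two months rather than monthly.

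**The case against.** The strongest reply is that this is a pilot whose primary outcomes are feasibility. Hypertension status is one of several secondary outcomes, reported descriptively without tests, and Data Analysis does not single it out for an effect estimate or for sizing the next trial. Earlier detection is also the intended mechanism, so more detected cases would be a real effect of monitoring. All of this stands. It lowers the severity and narrows the harm to reading detection as incidence or as treatment effect. It does not rescue the sentence in Blinding, because a count driven by how hard one looks is not protected by an objective instrument.

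Several stronger readings are tempting, and the article does not support them:
- **That a higher intervention count is all but guaranteed.** The lowest scenario gives 1%. All scenarios rest on assumed blood pressure distributions and on adherence that the pilot itself is testing.
- **That the alert probabilities are false-positive rates for the outcome.** The outcome definition does not say which readings count.
- **That control women have only three or four readings.** High-risk women may be referred to specialised care, and health workers counsel both arms to make at least four antenatal visits. The 31% attendance figure is national background, not a trial figure.
- **That self-rated acceptability shows bias between arms.** Only the intervention arm rates it, so it cannot distort a comparison, and the Discussion already discloses its subjectivity.
- **That facility and antenatal records would equalise ascertainment.** They would not, because the study's blood pressure and symptom triggers operate in one arm.

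Perinatal data may come from the woman herself, but from one checklist with no arm distinction. Reporting bias there is possible, not shown.

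**Conclusion.** The point holds in a limited form. The claim of objective outcomes and minimal bias is contradicted by the article's own description of how hypertensive disorders come to light. Detection differs by arm by design: at least 238 to 294 scheduled device readings (assuming delivery at 37 to 41 weeks and full adherence), with weekly symptom enquiry and two extra referral triggers, against antenatal-care readings alone. Hypertension status and the adverse consequences conditional on it are open to detection bias. For hypertension status the probable direction is a higher count in the intervention arm, and the conditional count of adverse consequences inherits the same pull.

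The size cannot be derived from the article, because the readings that define the outcome, the blood pressure distribution, adherence and the number of control readings are not given. The feasibility outcomes are not affected. This should be fixed, but it is not critical: the outcomes concerned are secondary and descriptive, in a pilot.

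**What to change.** - **Blinding.** Limit the statement on objectivity and minimal bias to outcomes measured alike in both arms. Acknowledge detection bias for hypertension status and its adverse consequences, and possible reporting bias for self-reported perinatal data.
- **Outcome Measures (Secondary) and Data Analysis: hypertension.** Report it by arm under the label *detected hypertension*, from antenatal, facility and discharge records abstracted with one checklist. State that detection still differs because referral triggers differ by arm. Do not use it as an effect estimate or as an incidence rate for the definitive trial.
- **Adverse consequences.** Count maternal and fetal complications in all randomised women from a common origin of 20 weeks, not only in those with detected hypertension.
- **Device blood pressure, heart rate and weekly symptoms.** Report these for the intervention arm only.

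Cost: changes of wording, one common abstraction checklist, and abstraction of complications for every randomised woman (70 records at most). Enrolment is complete, and none of this alters what participants receive. The price is that the pilot claims no between-arm effect on hypertension incidence or blood pressure, which the described data could not support in any case.

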#### Intervention

Before 20 weeks of gestation, each woman in the intervention arm will be provided with a Health Gauge device and with a smartphone, if she does not already have one. The app for Health Gauge will be installed on each participant’s smartphone. The women will be asked to use the Health Gauge device and app to measure their blood pressure at least two times a day (morning and evening), starting from 20 weeks of gestation. The blood pressure measurement records will be automatically stored in the smartphone app. Participants will be trained to charge and operate the Health Gauge device. Most women in rural Matlab do not have internet access. Hence, trained health workers will visit the women weekly and synchronize the smartphones with tablet computers to collect the stored data and to upload the data to an online server. The health workers will also measure the weight of the participant using a digital weighing scale every month. If any woman is found to be hypertensive (blood pressure is greater than or equal to 140/90 mmHg on two consecutive measurements), is presenting signs and symptoms associated with hypertensive disorders or associated complications (described later), or is gaining weight outside of the applicable US Institute of Medicine recommended range [11], she will be advised to visit Matlab hospital (icddr,b) or a government health facility immediately for further evaluation and management. If the condition demands, our health worker will ensure that an appropriate referral is made to a tertiary health care facility. This intervention will be in addition to the conventional programs offered by icddr,b as well as government health facilities.

In conventional care, women without any major risk factors, danger signs, or health conditions should visit a health facility four times during the antenatal period (at 8 to 12 weeks, 24 to 26 weeks, 32 weeks, and 36 to 38 weeks, with an additional visit at 41 weeks if they have not yet given birth). Pregnant women are separated into two groups by their care requirements—those eligible to receive routine care and those who require special care based on their health conditions or risk factors. Women with risk factors or special conditions are referred to a specialized clinic or hospital for further evaluation, and care is continued according to a specialist's advice. Women who are initially referred to a specialist may be subsequently considered eligible for routine care and women who are initially enrolled in routine care may later need to be referred for specialized care [19].

